### Data Collection and Monitoring

Aggregate- and individual record-level data will be analyzed over the course of the study period to assess the effect of the intervention on patient outcomes, health service efficiency, and the cost of providing emergency care. Our analysis will include aggregate KPI data, record-level health administrative data, and aggregate financial data and will be provided to the research team by the Newfoundland and Labrador Centre for Health Information. The ED KPIs (ie, LOS, PIA, and LWBS) used as the primary outcomes for this study are further described in Table S1 in Multimedia Appendix 1 alongside other variables that will be used for statistical modeling. Each of the primary outcomes will be calculated and assessed monthly over the course of the study period. The total number of monthly ED visits will be used as the denominator for our cluster-level summaries.

Individual record-level health administrative data will include demographic variables (eg, sex, date of birth, and postal code), mortality data, wait times data, diagnosis data, and triage acuity scores, among other variables. These data will be used to create aggregate KPI and financial data provided by Newfoundland and Labrador Centre for Health Information and to assess the intervention’s impact on the type and volume of patients who visit one of the 4 selected ED sites during the study period. Financial data will capture expenditures for staff, supplies, and procedures originating from the ED and will include data related to pharmacy, diagnostic imaging, laboratory testing, surgical day care, operating room procedures, physician salaries, physician fees for service claims, nurse salaries, administrative staff salaries, ambulance services, and other related ED costs.

Patient-reported experiences and patient satisfaction survey data will be collected 3 to 5 days after ED discharge via a telephone interview conducted by a research assistant who is also an EH employee. No identifiable information related to their ED visit will be collected during the survey, and patient consent will be obtained before the interview through an implied consent process that does not require a signed consent form. We provide all study participants with the opportunity to request an informed consent document that can be provided by email or post mail and contains contact information for the principal investigator and project manager. To minimize the loss to follow-up, the research assistant will attempt to reach patients up to 3 times within 2 weeks of the initial attempt. The interview will take <30 minutes, using a questionnaire we created based on CIHI’s patient-reported experiences [38] and patient satisfaction surveys for EDs [39]. Although most of Newfoundland and Labrador’s population is English speaking (97%) [40], language was not considered an exclusion criterion. Patient interview responses will be stored via Qualtrics (a web-based survey program), where research team members will be able to analyze the data while maintaining patient anonymity. An important consideration for this approach is that the only ethically approved means of contacting patients is by telephone using patient contact information at EH. Other options were explored such as surveying patients directly in the ED, but it was deemed unsuitable, as many patients are not likely to be in a physical or mental state conducive to participating in a study.

Beyond the data provided by traditional provincial data custodians, we will also consider the SurgeCon platform’s routinely collected aggregate data. These data include calculated SurgeCon levels, ED beds, bed availability, patient acuity, and patient process tracking. The SurgeCon action-based protocol is subdivided into 5 levels of escalation and is used to indicate the level of demand, availability of resources, and capacity in the ED. The levels range from 1 (optimal operating conditions) to 5 (very busy or patient surge). They are calculated using several variables such as ED and inpatient unit bed availability, resource shortages, and number of patients in the waiting room left to be triaged or seen by a physician, among many other options. A charge nurse or other frontline staff manually enter variables used by SurgeCon’s algorithm to determine SurgeCon levels via a data entry portal. Any data entered into the data entry portal will be made accessible to the research team through the creation of a special user role that provides access to all site-specific information and the ability to export collected data.

Our implementation strategy includes the operationalization of routine data capturing by charge nurses. The research team will regularly monitor data quality and completeness across all study sites. We will be working with frontline health care staff at each of the sites to find solutions when sites are found to be missing data entry intervals or if data quality is low. We are exploring opportunities to automate data collection for certain variables if they are found to be feasible and appropriate.

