### Study Aim and Objectives

In this study, we present the protocol for a 31-month SW-CRT trial. Our aim is to evaluate the performance of the SurgeCon platform in improving important patient and service process outcomes in EDs in an RHA in Newfoundland and Labrador and develop strategies to promote its scalability, sustainability, and successful implementation across the Canadian health system. The primary objective of the trial is to evaluate the effects of SurgeCon on ED performance by assessing its impact on LOS, PIA, and LWBS. The secondary objective of the trial is to assess the intervention’s impact on patient satisfaction and patient-reported experience with ED wait times and its ability to create better-value ED services by reducing ED costs.

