### Sample Size

On the basis of the results of a pilot study conducted at a rural ED site in EH’s jurisdiction, we established a common framework for optimal sample size calculations when the number of clusters available for randomization is limited to 4 sites for the SW-CRT design. We chose 1 cluster, which will cross over to an intervention state at a randomly assigned step. To keep things relatively simple, we assume that an equal number of observations is sampled in each cross section of each cluster. Alternatively, we expect an equal amount of observations per period per cluster. Results from our pilot study show a 15% to 30% decrease in the LOS or wait times between 6 and 30 months after SurgeCon implementation [30-32]. This trial is powered to detect a 15% change in LOS at 5% of type I error and 80% power with an ICC [33] of 0.1 for repeated measures (6 measures per step). A 10% reduction in ED wait time in the study sites could result in 10-minute reduction in LOS. To detect this change, a minimum sample size of N=20,280 (169/month/hospital for 30 months and 4 hospitals) is required. To be able to conduct age, sex, and patient acuity subgroup analyses for all ED visits across the 4 intervention sites, we will include all ED visits for this portion of the analysis as there is a low cost associated with extracting data from existing ED repositories, which routinely capture patient record-level information. For patient satisfaction, the study is powered to detect a 30% change in patient-reported experience measures or patient satisfaction [34-37] at a 5% of type I error and 80% power with an ICC of 0.1. Therefore, a sample size of 1320 (11/month/hospital for 30 months and 4 hospitals) would be sufficient for this study. Considering a 50% response rate, we will conduct 25 surveys per month per hospital. In particular, we demonstrated the required sample size and power calculation procedure with illustration for different combinations of the ICC to detect the standard effect size. For this illustrative purpose, we consider a clinical trial powered to detect a 10% to 30% reduction in wait times on a continuous scale at the 4 different EDs with 5% of type I error rate and 80% power.

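### Three co-equal primary outcomes, with error rate and power stated only for LOS and no success rule in the article: 5% and 80% cannot both describe the primary objective unless the outcomes are almost perfectly correlated

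*Protocol article*

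**What the plan says.** The primary objective (Study Aim and Objectives) is to "evaluate the effects of SurgeCon on ED performance by assessing its impact on LOS, PIA, and LWBS". The Abstract gives the same three measures under one primary objective. Data Collection and Monitoring again treats all three as primary, referring to "The ED KPIs (ie, LOS, PIA, and LWBS) used as the primary outcomes for this study", and Statistical Analysis applies the primary mixed model to monthly cluster summaries of each. The results are to include an effect size and its precision for every outcome. None of these sections ranks the three or says what pattern of results counts as success.

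The Sample Size section says: "This trial is powered to detect a 15% change in LOS at 5% of type I error and 80% power". The resulting figure is "a minimum sample size of N=20,280 (169/month/hospital for 30 months and 4 hospitals) is required". PIA and LWBS are not named with an effect size, an error rate or a power. The 5% and 80% pair appears twice more in that section. One use is for a secondary outcome: "the study is powered to detect a 30% change in patient-reported experience measures or patient satisfaction". The other is an illustration: "we consider a clinical trial powered to detect a 10% to 30% reduction in wait times on a continuous scale". The illustration does not name PIA and, being on a continuous scale, cannot cover LWBS, which is a proportion.

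**The concern.** Which outcomes are primary, and which of them carries the design error rate and power, are choices that the article itself makes. It makes them unevenly: three outcomes of equal standing, with operating characteristics for one.

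The practical risk is a mixed result. Table 1 describes a component aimed directly at shortening PIA, so an improvement in PIA without a clear change in LOS is a realistic outcome. The article does not say whether that would show an effect on ED performance. The Introduction says the trial is to generate data supporting more comprehensive implementation, so the reading of a mixed result should not be left open until the results are known. Each primary outcome is also to be assessed monthly during the study, so results may be seen before the rule is settled.

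**Working it through.** **Inputs from the article.** Three primary outcomes; 5% type I error and 80% power for LOS; 169 visits per month per hospital, 30 months, 4 hospitals.

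**Assumptions.** Two-sided tests (sidedness is not stated); test statistics approximately normal with a common pairwise correlation r, which the article does not give; for joint power, 80% for each of PIA and LWBS, which is also not stated.

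**The plan's own figure.** 169 × 30 × 4 = 20,280, as stated. The 169 itself cannot be derived, because no patient-level standard deviation of LOS is given. This does not affect the calculations below.

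**Reading A: success on any one outcome counts, each tested at 5%.**
- Independent outcomes: 1 − 0.95³ = 1 − 0.857 = 0.143.
- Upper bound under any dependence: 3 × 0.05 = 0.15.
- Correlated outcomes: the probability that at least one of three null statistics exceeds 1.96 in absolute value.

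**Reading B: all three must succeed.**
- The false positive rate stays at or below 5%, because at least one true null hypothesis must be rejected at 5% for a false claim.
- Joint power with independent outcomes: 0.80³ = 0.512.
- Correlated outcomes: the probability that three statistics, each with mean 1.960 + 0.842 = 2.802, all exceed 1.96.

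| Correlation r | A: at least one false positive | B: joint power, 80% each |
|---|---|---|
| 0 | 14.3% | 51% |
| 0.5 | 12.5% | 61% |
| 0.8 | 9.8% | 69% |
| 0.9 | 8.4% | 72% |
| 1 | 5.0% | 80% |

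**Which correlations are plausible.** For a patient who is seen, the time to PIA is part of LOS, and leaving without being seen depends on the wait. In the pilot (Background), PIA fell by 104.3 − 42.2 = 62.1 minutes and LOS by 199.4 − 134.4 = 65.0 minutes, and LWBS fell as well. This does not measure the correlation of the test statistics, but it points to strong dependence. I therefore take r = 0.8 to 0.9 as the more plausible range, and independence as an extreme.

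**Cost of two remedies.**
- Bonferroni: 0.05/3 = 0.0167 per outcome. LOS power at N = 20,280 falls from 80% to about 66%. Keeping 80% multiplies N by 1.334, to about 27,050.
- Fixed sequence starting with LOS: LOS is still tested at 5% with 80% power at N = 20,280. A false claim requires rejecting the first true null in the sequence, which happens with probability at most 5%, so the error over all three is at most 5%.

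**The case against.** The strongest reply is that this rests partly on silence. The full protocol and the statistical analysis plan are not shown, a multiplicity rule is often placed there, and the article refers readers to Multimedia Appendix 1 for outcome definitions and methodological issues. This stands as far as it goes: one can say only that no ordering or success rule appears in this article. It does not dispose of the point, because the article itself gives three outcomes equal primary standing and attaches error and power to one.

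A reader might infer that the trial's overall error exceeds a trial-wise 5% that the article promises. The text does not support this. Its 5% belongs to the LOS calculation, no familywise rate is stated, and the excess arises only if success on any one outcome counts, a rule the article does not give. Under an all-three rule there is no inflation at all. It would also be too strong to lead with 14.3%, since independence is the least plausible case here.

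Nor is it right that 5% and 80% are given for LOS and nothing else. They are also given for patient satisfaction and for the wait-time illustration. Among the named primary outcomes, however, LOS is the only one.

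Finally, a fixed sequence lowers the standing of PIA and LWBS, and the first site began implementation in September 2021, with monthly interim analyses planned. A change at this stage is therefore more than wording and carries a risk of bias if made with results in view. That is a fair condition on how the change is made.

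**Conclusion.** The point holds in conditional form. The article leaves open whether one or all three primary outcomes must succeed, and each reading loses one of the two stated design properties. If any one suffices, the chance of a false positive is about 8% to 10% at correlations of 0.9 to 0.8, and 14.3% under independence. If all three are required, joint power is about 69% to 72% at correlations of 0.8 to 0.9. Only near-perfect correlation would let 5% and 80% both describe the primary objective.

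The sizes rest on assumed correlations, two-sided testing and, for joint power, an assumed 80% for PIA and LWBS. An unseen document may already contain a rule; if so, the article should state it. The monthly interim analyses are a separate possible source of inflation and are not counted here.

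**What to change.** Designate LOS, the outcome the trial is powered on, as the first confirmatory test at 5%. Then test PIA and LWBS in that fixed order, each at 5% and only if the previous test is significant. Report all three estimates with confidence intervals whatever the test results; the article already plans to give effect size and precision for each outcome. In Sample Size, describe the 5% and 80% as applying to LOS.

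Record the change as a dated amendment to the protocol and the registry entry, with a statement that it was made without reference to interim results.

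The cost is the amendment itself. No patients are added and LOS keeps its planned power. The downside is that PIA and LWBS carry no confirmatory claim if LOS is not significant, even where the intervention has shortened PIA. If the investigators prefer another order or an all-three rule, stating it in advance would also close the gap, but they should then give the power that goes with it.

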**Objective:**

The primary objective of this trial is to determine the effects of SurgeCon on ED performance by assessing its impact on length of stay, the time to a physician’s initial assessment, and the number of patients leaving the ED without being seen by a physician. The secondary objectives of this study are to evaluate SurgeCon’s effects on patient satisfaction and patient-reported experiences with ED wait times and its ability to create better-value care by reducing the per-patient cost of delivering ED services.

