We have created a quality improvement intervention called SurgeCon. As a pragmatic ED management platform, SurgeCon includes 3 separate components (described below) that together act to decrease wait times and improve the sustainability of Newfoundland and Labrador’s ED services without significant workforce changes. These interventions include restructuring the ED organization and workflow, fostering a patient-centric environment, and quantifying ED demands and available resources in real time. SurgeCon is designed to enable frontline health care workers to anticipate and mitigate surges in patient volume through a series of proactive steps and decision-making tools. SurgeCon attracted the attention of the Newfoundland and Labrador Eastern Health (EH) RHA after they missed their own ED wait time benchmarks in 2016 [22]. The initial development of the SurgeCon intervention came about after an external review was completed by an independent third party to determine which areas of ED operations could be adjusted to improve wait times and departmental efficiency. The external review was one of many components included in a provincial wait time reduction initiative [23].

We piloted SurgeCon at the ED located in Carbonear, Newfoundland and Labrador, an EH administered hospital, over 45 months from July 1, 2013, to March 31, 2017. Data from the pilot study were analyzed using an interrupted time series analysis to assess its effect on ED performance. The resulting change in indicators was noteworthy, despite a 25.7% increase in patient volume. Over the course of the 45-month pilot study, average time to physician’s initial assessment (PIA) decreased from 104.3 (SD 9.9) minutes to 42.2 (SD 8.1) minutes, length of stay (LOS) in the ED decreased from 199.4 (SD 16.8) minutes to 134.4 (SD 14.5) minutes, and the number of patients LWBS decreased from 12.1% (SD 2.2%) to 4.6% (SD 1.7%). All of these changes were statistically significant. The marked and sustained impact of SurgeCon on ED performance in Carbonear supports the case for its extension to other EDs.

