The primary method of analysis used in this study is GLMM, which will consider monthly cluster-level summary measures such as means of LOS, PIA, or proportion of LWBS. Our GLMM models will include fixed effects for time, intervention effects, random effects, and random time effects for each cluster. In addition, ED setting (rural or urban), ED volume, and size of ED administrative resource will be added as cluster-level covariates. For secondary outcomes such as patient-reported experience and satisfaction, our individual-level GLMM models will include fixed effects for time, intervention effect, and random effects and random time effects for each cluster, with the covariates consisting of age, gender, the reason for ED visit, and cluster-level LOS, PIA, and proportion of LWBS.

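### The stated denominator, total ED visits, does not fit mean PIA: taken literally it counts patients who leave unseen as zero-minute waits and attenuates the PIA effect when LWBS falls

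*Protocol article*

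**What the plan says.** Data Collection and Monitoring names LOS, PIA and LWBS as the primary outcomes, says each is calculated monthly, and then gives a single rule: "The total number of monthly ED visits will be used as the denominator for our cluster-level summaries". It makes no exception by outcome.

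The Analyses section says that the primary mixed model works on "monthly cluster-level summary measures such as means of LOS, PIA, or proportion of LWBS". Mean PIA is therefore one of the cluster-level summaries to which the rule applies.

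The abstract's objective describes LWBS as "the number of patients leaving the ED without being seen by a physician". Such a visit has no time to physician assessment.

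The article also says that the three indicators "are further described in Table S1 in Multimedia Appendix 1 alongside other variables that will be used for statistical modeling". That table is not available here.

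**The concern.** Total visits is the natural denominator for the LWBS proportion. It is not a valid denominator for a mean of PIA, because some of the visits it counts have no PIA value. Dividing the summed PIA times by all visits is the same as giving every LWBS patient a wait of zero.

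If the LWBS share were constant, this would only rescale PIA. But SurgeCon is meant to reduce LWBS, so the share of artificial zeros would be larger in control months than in intervention months. Success on LWBS would then push the PIA summary upwards, against the intervention. The fixed time effects and cluster random effects in the model do not remove this, because the distortion moves with treatment status. Cluster-level PIA is also a covariate in the planned patient-experience models, so the same quantity would carry over there.

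**Working it through.** **The plan's own figures.** The article reports no figure that uses the PIA denominator, so there is none to reproduce on this point. The stated sample size (169 × 30 × 4 = 20,280) is for LOS and does not depend on it.

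**Inputs.**
- Pilot PIA (Background): "decreased from 104.3 (SD 9.9) minutes to 42.2 (SD 8.1) minutes". Assumption: these are means among patients seen.
- Pilot LWBS (Background): 12.1% before, 4.6% after.
- Planning range (Sample Size): "we consider a clinical trial powered to detect a 10% to 30% reduction in wait times on a continuous scale".

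**Formula.** With all visits as denominator,

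summary = (mean PIA among patients seen) × (1 − LWBS).

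If r is the true relative reduction among patients seen,

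apparent reduction = 1 − (1 − r) × (1 − LWBS after) / (1 − LWBS before).

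**At the pilot effect.**
- Patients seen: 104.3 to 42.2 minutes, a fall of 62.1 minutes, or 62.1/104.3 = 59.5%.
- All visits: 104.3 × 0.879 = 91.7 and 42.2 × 0.954 = 40.3, a fall of 51.4 minutes, or 51.4/91.7 = 56.1%.

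The gap in minutes is 62.1 − 51.4 = 10.7. Of this, 62.1 × (1 − 0.879) = 7.5 minutes comes from rescaling both periods by the baseline share seen. Only 42.2 × (0.954 − 0.879) = 3.2 minutes comes from the change in LWBS. The relative figures are therefore the fairer guide to the distortion.

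**At smaller effects.** The result depends on how far LWBS falls alongside PIA. Three cases:

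| True PIA reduction | LWBS falls in proportion to PIA, from 12.1% (assumption) | LWBS 5% to 3% (assumption) | LWBS 12.1% to 4.6% (full pilot fall) |
|---|---|---|---|
| 10% | 8.8% | 8.1% | 2.3% |
| 15% | 13.2% | 13.2% | 7.7% |
| 30% | 27.1% | 28.5% | 24.0% |

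The 15% row in full:
- Proportional: LWBS after = 12.1% × 0.85 = 10.3%; 1 − 0.85 × 0.897/0.879 = 13.2%.
- 5% to 3%: 1 − 0.85 × 0.97/0.95 = 13.2%.
- Full pilot fall: 1 − 0.85 × 0.954/0.879 = 7.7%.

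In the last column the fall in LWBS alone multiplies the summary by 0.954/0.879 = 1.085. A true reduction would have to be below 1 − 0.879/0.954 = 7.9% to appear as an increase.

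**The case against.** **The definition may sit elsewhere.** Which visits count towards PIA is a matter of variable definition, and the article sends the reader to Table S1 for that. The aggregate indicators are also supplied by the provincial data custodian, which may already average PIA over patients seen. This stands: it is not established that anyone intends to score LWBS visits as zero. It does not rescue the sentence, which is unqualified, comes directly after the three outcomes are named, and would contradict Table S1 if the table restricts PIA.

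**The wording may be meant for LWBS only.** The denominator sentence does not name PIA, and a denominator most naturally belongs to a proportion. That is a fair guess at the intention. But the sentence speaks of the cluster-level summaries in general, and the Analyses section lists mean PIA as one of them.

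**The larger distortions need an unlikely pairing.** The 2.3% and 7.7% results, and the 7.9% threshold, combine a modest PIA gain with the full pilot fall in LWBS, which was (12.1 − 4.6)/12.1 = 62% in relative terms. In the pilot that fall came with a PIA reduction of almost 60%. Nothing in the article supports so large an LWBS fall alongside a 10% or 15% PIA gain. This objection stands, and it governs the size of the finding.

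**LOS.** A reader might infer that LOS has the same fault. The article says nothing about missing departure times for LWBS patients, and total visits can be defended for LOS where those times exist. The sample size is also untouched, since "This trial is powered to detect a 15% change in LOS at 5% of type I error and 80% power with an ICC" concerns LOS.

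**Conclusion.** The point holds as a defect in a stated rule, with a modest likely effect. Followed as written, the denominator couples mean PIA to LWBS and biases the PIA comparison against SurgeCon. On the assumption that the pilot values are means among patients seen, the loss is small at the pilot effect. It is about two percentage points at a true 15% reduction under either of the two smaller LWBS falls assumed above, and about seven points only under the full pilot fall in LWBS.

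A reader might infer that the rule would hide SurgeCon's benefit or turn it into apparent harm. The documents do not support that. Reversal needs a true PIA reduction below 7.9% together with the full pilot fall in LWBS, and the smallest reduction in the planning range is 10%. The finding is also conditional on Table S1: if the table already limits PIA to patients seen, what remains is an inconsistency in the main text.

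**What to change.** Replace the denominator sentence with one that separates the outcomes: total monthly visits for the LWBS proportion; visits with a recorded physician assessment for mean PIA; visits with a recorded departure time for mean LOS. If Table S1 already says this, bring the main text into line with it.

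Add that PIA is to be interpreted together with LWBS. Averaging over patients seen removes the arithmetic link but not possible selection: those who formerly left may be long waiters, so the mix of patients seen may change as LWBS falls. A sensitivity analysis of time to assessment with LWBS as a competing event would address this, but it is optional.

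The cost is a sentence or two. The record-level wait-time data are already to be obtained, and neither the design nor the sample size changes.
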